#### Outcome: frequency of antimicrobial prescribing and consumption

The frequency of antimicrobial prescribing will be compared between the control and each intervention arm (arms A and B).

• Consultations will be analyzed according to whether an antimicrobial was prescribed or not (yes/no).

• The prescription rates per group per month for each antimicrobial group will be calculated as the number of antimicrobial prescriptions per 1,000 consultations per month.

• Comparison of the overall reduction over the period of the intervention will be based on the percentage of consultations where an antimicrobial was prescribed at the start of the intervention, as compared with the end.

The frequency of antimicrobial consumption will be compared between intervention arms A and B, according to their response to the text messages.

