#### Secondary outcome: decrease in the quantity of consumption (control - intervention arm B)

To estimate the potential power to detect this secondary outcome, an additional sample size calculation was carried out.

• 56% of the patients presenting with a UTI, and for whom a urine sample was submitted for microbiological analysis, received a prescription
[8].

• A 20% decrease in consumption can be achieved through delayed prescribing
[42].

Taking account of the cluster effect and based on previous ICC estimates, a total sample size of 240 patients recruited from 20 practices gives a power of 80% to detect a significant change in the proportion of patients who reduce antimicrobial consumption through delayed prescribing if the ICC is 1%.

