#### The control arm

To gather comparable data on UTI consultations, practices in the control arm will complete a coding workshop at the beginning of Phase 1. For the remainder of the intervention, the control arm will provide 'usual care’ and will receive their audit and feedback reports at the end of intervention Phase 3. Practices in the control arm will also submit urine samples from UTI patients and request patients’ mobile telephone numbers for the duration of the intervention.

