#### Follow-up data

Evaluative information from the patients will be obtained via text message. These text messages will require a minimal response (at no cost) from the patient and will be used to assess actual consumption of the prescribed antimicrobial. Patients can discontinue receiving these text messages at any time by replying STOP.

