### Method of quantitative data analysis

Quantitative analysis will be undertaken using SPSS for Windows release 20.0 (SPSS Inc., Chicago, IL, USA) and Stata 11 (Stata Corporation, Texas). Multilevel analysis will be performed using MLwiN version 2.21 software and cost-effectiveness analysis will be conducted using Excel and Stata 11. Statistical significance will be set at the 5% level for all outcomes.

Multivariate analysis will examine intervention and control arm changes from baseline measures and will follow the principle of intention to treat. Outcomes will be compared between intervention (arms A and B) and the control arm, using a multilevel logistic modelling approach to control for baseline prescribing as well as other confounding variables at patient and practice level. All statistical analysis will be undertaken in accordance with current guidelines for randomized controlled trials
[71].

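### Antimicrobial consumption is powered as control versus arm B, but its outcome-specific analysis compares arm A with arm B; the scale and denominator of the 20% decrease also need stating

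*Protocol article*

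**What the plan says.** Under *Sample size*, the consumption calculation is headed "Secondary outcome: decrease in the quantity of consumption (control - intervention arm B". It takes 56% of sampled UTI patients receiving a prescription as the starting point, adds that "A 20% decrease in consumption can be achieved through delayed prescribing", and concludes that "a total sample size of 240 patients recruited from 20 practices gives a power of 80" (per cent) at an ICC of 1%.

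Under *Outcome: frequency of antimicrobial prescribing and consumption*, prescribing is compared between control and each intervention arm. Consumption is then treated differently: "The frequency of antimicrobial consumption will be compared between intervention arms A and B, according to their response to the text messages".

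Three other places bear on the choice:

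- *Method of quantitative data analysis*: "Outcomes will be compared between intervention (arms A and B) and the control arm, using a multilevel logistic modelling approach".
- *The control arm*: "Practices in the control arm will also submit urine samples from UTI patients and request patients’ mobile telephone numbers for the duration of the intervention".
- *Follow-up data*: the text messages "will be used to assess actual consumption of the prescribed antimicrobial".

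**The concern.** Consumption is part of the trial's stated aim and of secondary objective 1. For this outcome the article names the comparison in two places, and the two do not agree. Because both are fixed in the article, this is not a detail left open for an analysis plan.

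The two contrasts answer different questions. Control versus B asks whether the full arm B package lowers consumption against usual care. A versus B asks what the delayed-prescribing component adds to a package that already includes the workshop, prompts, feedback and leaflets. The stated 80% power belongs to the first question only. The article also says that the data analysis will not be blinded (*Limitations of the study*), so the choice of contrast should not still be open when data arrive.

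A smaller matter is that the primary calculation calls its 10% absolute, while the consumption calculation gives its 20% no scale. From a baseline of 56%, the two readings lead to very different sample sizes.

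**Working it through.** **1. The contrasts side by side**

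| Place in the protocol article | Comparison for consumption |
|---|---|
| *Sample size*, secondary outcome | control v B |
| *Outcome: frequency of antimicrobial prescribing and consumption* | A v B |
| *Method of quantitative data analysis* (all outcomes) | A and B v control |
| *Quantitative data analysis*, opening paragraph (all data) | each arm |

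Only the outcome-specific sentence leaves control out, and no reason is given. The neighbouring outcome, the effect of delayed prescribing, is compared between B and control.

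**2. Reproducing 240**

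Inputs from the article: baseline 56%, 20 practices, ICC 0.01, alpha 5%, power 80%. My assumptions: two-sided test, 10 practices per arm, equal practice sizes.

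Reading the 20% as percentage points, 56% to 36%:

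- Pooled formula: n = [1.96·√(2 × 0.46 × 0.54) + 0.8416·√(0.2464 + 0.2304)]² / 0.20² = 96.3, so 97 per arm. With continuity correction, 107 per arm.
- Clustering: with m patients in each of 10 practices per arm, 10m = n[1 + 0.01(m − 1)], so m = 0.99n / (10 − 0.01n).
- For n = 107: m = 105.93 / 8.93 = 11.86, rounded up to 12. Total 20 × 12 = **240**, the stated figure.
- Without continuity correction the total is 204 (unpooled) to 213 (pooled), or 220 after rounding m up.

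**3. Power at 240, percentage-point reading**

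Design effect 1 + 11 × 0.01 = 1.11. Effective n per arm 120 / 1.11 = 108.1.

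z = 0.20 / √(0.4768 / 108.1) − 1.96 = 1.05, giving about **85%** power (81% with continuity correction).

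**4. The relative reading, 56% to 44.8%**

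- z = 0.112 / √(0.4937 / 108.1) − 1.96 = −0.30, giving about **38%** power at 240 (33% with continuity correction).
- Unpooled n for 80% power = 7.849 × 0.4937 / 0.112² = 308.9 per arm; m = 305.8 / 6.911 = 44.25; total **885**.
- With continuity correction the total is about **970**.
- A one-sided test still needs 660 to 720 after rounding m up.

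No version of the relative reading from 56% comes near 240. A 20-point fall from 56% is a relative reduction of 0.20 / 0.56 = 36%.

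**5. The denominator**

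The 56% is the share of sampled UTI patients who were prescribed an antimicrobial. The text messages ask about taking a prescribed antimicrobial. If the denominator is all UTI patients, 56% is a usable upper starting value for consumption. If it is prescribed patients, 56% is not their baseline, and the article gives none. The sample-size text also speaks of the proportion who reduce consumption, while the analysis text speaks of the frequency of consumption.

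**The case against.** Three objections carry weight.

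**Comparison with control is not excluded.** A reader might infer that the trial can no longer say whether arm B lowers consumption against usual care, and that the control text-message data will go unused. The article does not support that. Its general analysis statements provide for comparison with control for all outcomes, and the A versus B sentence does not say it is the only comparison. What stands is narrower: a general and a specific statement conflict, and an analyst could defend following either.

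**The 240 is not an error.** A reader might infer that it is too small. It reproduces on the percentage-point reading, which is also the scale of the primary calculation. It is a number sufficient for 80% power, not a cap. *Feasibility* expects 2,038 prescribed patients from 20 practices; at the 72% participation cited in the *Background* that is up to 2,038 × 0.72 = 1,467 responders. Mobile-number capture is unknown, so this is an upper figure. Even the relative reading from 56% would have about 83% power at 1,000 responders. And if the denominator were prescribed patients with a higher baseline, 240 could nearly suffice on the relative scale: an assumed 80% falling to 64% gives about 76% power. The 38% therefore holds only with 56% as baseline and 240 as the achieved number.

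**The power of A versus B cannot be fixed from the article.** A reader might infer that this contrast is underpowered because arm A patients also receive material on antimicrobials. No arm A effect on consumption is given. With arm B at 36% and 240 patients, assumed arm A values of 54% down to 46% give 77% down to 32% power, a range too wide to support a claim.

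**Conclusion.** The mismatch is real: consumption is powered for control versus B, and its own analysis paragraph specifies A versus B, against the general rule that outcomes are compared with control. It concerns a secondary outcome and is put right by wording. It does not affect the primary comparison, and it does not mean that the question against usual care is lost.

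The scale of the 20% is a clarification. Given the 56% baseline, 240 corresponds to 56% versus 36% with about 85% power. A 20% relative fall from that baseline would have about 38% power at 240 and need roughly 885 to 970 responders. These figures assume a two-sided 5% test, 10 equal practices per arm and an ICC of 1%. The denominator needs one definition, because the baseline is a prescribing rate and the measurement is of consumption.

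**What to change.** - In *Outcome: frequency of antimicrobial prescribing and consumption*, name control versus arm B as the main consumption comparison, using the text-message responses from both arms. Keep A versus B as an additional contrast that isolates delayed prescribing.
- In the secondary-outcome calculation under *Sample size*, state that the 20% is in percentage points (56% versus 36%) and that 240 means patients with text-message consumption data. If a relative fall was intended, restate the power at 240 as about 38%, or give the required number.
- Define the outcome once, as a proportion of all UTI patients or of prescribed patients, and use that denominator in both sections. If it is prescribed patients, supply a baseline for them in place of 56%.

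The first two changes, as set out, are wording only: control practices are already asked to request mobile numbers throughout the intervention, so no new data collection is needed. Choosing prescribed patients as the denominator would also require a short recalculation.

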#### Outcome: the effect of delayed prescribing

The frequency of delayed prescribing measured as a percentage of overall prescribing for UTIs will be compared between the intervention arm B and the control. Compliance with delayed prescriptions will be measured by the percentage of patients who waited the recommended 48 hours (information obtained by text message).

#### Outcome: reconsultation visits

Reconsultation will be determined by the number of reconsultation UTI visits to the GP within one month of initial treatment.

##### Outcome: change in cognitive beliefs (knowledge and attitudes)

Change in cognitive beliefs at the start of Phase 1 to the end of Phase 3 will be assessed by comparing the percentage change in cognitive beliefs (knowledge and attitudes) relating to antimicrobial prescribing behaviour between the three arms.

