#### Secondary objectives

1. To compare the effect of the intervention on the frequency of antimicrobial prescribing and antimicrobial consumption in patients presenting with a UTI.

2. To measure the uptake and impact of delayed antimicrobial prescribing for UTIs and the impact of this treatment approach on UTI GP reconsultation visits.

3. To assess a change in cognitive beliefs (knowledge and attitudes) of GPs related to antimicrobial prescribing.

4. To conduct a cost-effectiveness and process evaluation of the SIMPle intervention.

5. To compare the prescribing rates of the intervention arms with regional UTI antimicrobial prescribing rates.

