### Practice identification and randomization

A list of all practices submitting urine samples to GUH was obtained and practices were contacted by phone to establish what patient management software system they used. Practices using the selected patient management software system were thereby identified. The first 30 practices were invited to participate by an invitation letter, which provided an overview of the study, benefits for participation and the contact details of the research team.

Within 10 days of receipt of this invitation, practices were telephoned to determine their interest and willingness to participate in the study. If a practice declined to participate, the reason for not agreeing was recorded and that practice was replaced by another from the eligibility list. This process continued until 30 practices were enrolled. Practices were then randomized to intervention and control arms, using a list of computer-generated numbers. The workshop facilitators were blinded to the allocation throughout the delivery of the coding workshops in Phase 1.

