#### Questionnaires

Additional information collection will take place at primary points throughout the intervention, including the administration of a questionnaire to collect data on knowledge and attitudes towards antimicrobial prescribing by GPs. This questionnaire will be administered to GPs at the beginning of Phase 1, at the coding workshop and at the end of Phase 3, to measure potential changes in knowledge, attitudes and behaviours of GPs in each arm. A practice profile will be completed at the beginning of Phase 1, to determine number of whole-time equivalent GPs and practice size.

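### GP beliefs are to be compared between arms as percentage change, and nothing says that each GP's Phase 1 value is adjusted for

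*Protocol article*

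**What the plan says.** The third of the secondary objectives is "To assess a change in cognitive beliefs (knowledge and attitudes) of GPs related to antimicrobial prescribing". Under Questionnaires, the timing is fixed: "This questionnaire will be administered to GPs at the beginning of Phase 1, at the coding workshop and at the end of Phase 3". The coding workshop itself takes place at the start of Phase 1, so there is one baseline measurement and one at the end of the patient phase.

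The outcome section on cognitive beliefs then states how the arms will be compared: by "comparing the percentage change in cognitive beliefs (knowledge and attitudes) relating to antimicrobial prescribing behaviour between the three arms". Neither the scoring of the questionnaire nor the meaning of percentage change is defined.

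The Method of quantitative data analysis section adds, for outcomes in general, that "Multivariate analysis will examine intervention and control arm changes from baseline measures" and that arms will be compared "using a multilevel logistic modelling approach to control for baseline prescribing as well as other confounding variables at patient and practice level". The significance level is 5% for every outcome.

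**The concern.** The belief questionnaire is collected before and after the intervention, so the baseline value is available as a covariate. The protocol instead makes the change, expressed as a percentage, the quantity to be compared.

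If that is a ratio formed for each GP, it has two weaknesses. It divides by a baseline measured with error, so GPs with low starting scores get undue influence. It also carries chance differences between arms at baseline into the result through regression to the mean. With 30 practices over three arms, about 10 per arm if split equally, some imbalance at baseline would not be surprising.

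The general methods section does not clearly repair this. The baseline it names is prescribing, and its other covariates are at patient and practice level, whereas beliefs are measured on GPs. What is at stake is precision, and how far a secondary result can be read at face value if the arms happen to start apart.

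**Working it through.** **Inputs from the protocol.** Two measurement occasions (Questionnaires); percentage change compared between three arms (outcome section on cognitive beliefs); 30 practices (Practice identification and randomization); 5% level (Method of quantitative data analysis). The protocol gives no sample size, standard deviation, effect size or power for this outcome, so there is no stated figure to reproduce. Every number below rests on assumptions.

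**1. Change score against baseline adjustment.** Assume a continuous score with the same variance σ² at both times, baseline-to-follow-up correlation r, and independent GPs.

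- Variance of a simple change: 2(1 − r)σ²
- Residual variance after adjusting for baseline: (1 − r²)σ²
- Proportional reduction: 1 − (1 − r²)/[2(1 − r)] = (1 − r)/2

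| r (assumed) | change | adjusted | reduction |
|---|---|---|---|
| 0.3 | 1.40 | 0.91 | 35% |
| 0.5 | 1.00 | 0.75 | 25% |
| 0.7 | 0.60 | 0.51 | 15% |
| 0.9 | 0.20 | 0.19 | 5% |

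**2. Effect of a chance imbalance.** Suppose there is no true effect and one arm starts 0.25 SD higher (assumed). The expected shift in the simple change contrast is −(1 − r) × 0.25 SD: −0.175 SD at r = 0.3, −0.125 SD at 0.5 and −0.075 SD at 0.7. Adjustment for baseline removes it.

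**3. Percentage change itself.** Step 1 concerns a simple change, which is not what the protocol names. A simulation therefore compared per-GP percentage change, simple change and baseline adjustment. Assumptions: two arms of 30 GPs, baseline mean 50, coefficient of variation (CV) 0.15 or 0.30, true effect 0.5 SD, two-sided 5%, clustering ignored, 3,000 replicates (2,000 under no effect). Power was:

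| r | % change, CV 0.15 | % change, CV 0.30 | simple change | adjusted |
|---|---|---|---|---|
| 0.3 | 34% | 24% | 36–38% | 50–51% |
| 0.5 | 45% | 33% | 48–49% | 58–59% |
| 0.7 | 66% | 51% | 69–70% | 76% |

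Percentage change had the lowest power in every case, and did worse with the larger spread. With no true effect, rejection rates were 3.8% to 5.8% across all three methods, so the level holds.

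**4. The other reading.** If the phrase means the change in the percentage of GPs who give a certain answer, there is no per-GP ratio and steps 1 to 3 do not carry over. A comparison of arm-level changes in percentages still makes no use of how each GP answered in Phase 1.

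**The case against.** The best reply is that the article never mentions a score. Neighbouring outcomes are percentages of consultations, prescriptions or patients, and a multilevel logistic model is prescribed for outcomes generally, which suits a proportion of GPs. On that reading the arguments about dividing by a baseline, and the variance figures, fall away. This stands: both readings are open, and the figures are conditional on one of them. For the same reason, a reader might infer that the logistic model is an error for this outcome. The article does not support that, because it does not say that the outcome is continuous.

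A second reply is that covariates for one secondary questionnaire outcome belong in the analysis plan, which was not available for this review, and that the outcome section does not say the comparison is unadjusted. This stands only in part. The article does not merely stay silent; it names percentage change as what is compared. The covariates it does list, "using a multilevel logistic modelling approach to control for baseline prescribing as well as other confounding variables at patient and practice level", do not include the GP's own baseline beliefs.

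Third, the correlations, effect size and number of GPs are all assumed, and clustering within practices is ignored. That is correct. All GPs in each practice are invited and no count is given, so it cannot be said that there are few of them.

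**Conclusion.** The point holds as a modest improvement to one secondary outcome. The protocol compares arms on percentage change in beliefs and does not state that the Phase 1 value is a covariate. If the outcome is a per-GP percentage change in a score, baseline adjustment is more precise and protects against chance imbalance. For scale, adjustment reduces variance by 15% to 35% relative to a simple change for r from 0.7 down to 0.3, and by only 5% at r = 0.9, given equal variances and independent GPs. Those percentages describe a simple change. The comparison with percentage change comes only from the simulation, under its own assumed inputs.

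A reader might go further and infer that the planned analysis would produce spurious findings. The calculations do not support that: the type I error stays near 5% over repeated randomisation. The sensitivity is conditional on an imbalance that may not occur. If the outcome is a percentage of GPs, what remains is that each GP's baseline response is not used. The primary conclusion is unaffected on either reading.

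**What to change.** In the outcome section on cognitive beliefs, define how the questionnaire is scored. Then state that end-of-Phase-3 beliefs will be compared between each intervention arm and control, adjusted for the same GP's Phase 1 value, with practice as a random effect. Use a linear mixed model if the outcome is a score and a multilevel logistic model if it is a yes/no item. Report each difference with its interval, and keep percentage change as a descriptive summary only.

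The cost is small, since both questionnaires are already planned and only the analysis wording changes. The one practical requirement is that each GP's two questionnaires can be linked, which the article does not say is done, so this needs confirming.

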#### Outcome: impact of patient educational material

A potential additional impact of patient education will be evaluated by comparing prescribing and consumption between A1 and B2 (no support) and A2 and B1 (support) (see Figure 
1).

### Method of quantitative data analysis

Quantitative analysis will be undertaken using SPSS for Windows release 20.0 (SPSS Inc., Chicago, IL, USA) and Stata 11 (Stata Corporation, Texas). Multilevel analysis will be performed using MLwiN version 2.21 software and cost-effectiveness analysis will be conducted using Excel and Stata 11. Statistical significance will be set at the 5% level for all outcomes.

Multivariate analysis will examine intervention and control arm changes from baseline measures and will follow the principle of intention to treat. Outcomes will be compared between intervention (arms A and B) and the control arm, using a multilevel logistic modelling approach to control for baseline prescribing as well as other confounding variables at patient and practice level. All statistical analysis will be undertaken in accordance with current guidelines for randomized controlled trials
[71].

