**GP focused**				
Coding workshop	All arms	Demonstrate the purpose of electronically coding UTI consultations using coding guidelines (International Classification of Primary Care code U71) and how to implement uniform coding in routine practice.	Promote routine uniform consultation coding for UTIs.	Gather baseline practice data and knowledge and attitudinal data (questionnaires).
Interactive workshop A	Intervention arm A	Raise the profile of GPs’ antimicrobial prescribing behaviours and their role in the broader issue of AMR.	Encourage GPs to become more aware of their antimicrobial prescribing behaviours through discussion of their role in the development of AMR.	Process evaluation
		Provide guidance on antimicrobial prescribing through adherence to guideline for UTI.		
Interactive workshop B	Intervention arm B	In addition to the core components of interactive workshop A, the recommendation to delay antimicrobial prescribing for UTIs facilitated through shared decision making will be promoted.		Encourage the use of delayed prescribing for UTIs.
				Process evaluation.
Electronic audit and feedback reports	Intervention arms A and B	A monthly report will be available (electronically) to practices summarizing their antimicrobial prescribing patterns for UTIs and antimicrobial resistance patterns of *E. coli*.	To provide a comparison of antimicrobial prescribing for UTIs between practices.	To provide an overview of antimicrobial resistance patterns in *E. coli* causing UTIs.
Stakeholder awareness		Information about the intervention and the issue of AMR will be provided to other stakeholders; pharmacists, practice receptionists and practice nurses.	To update all stakeholders on the overall aim of the intervention.	
Computer “prompt” application	Intervention arm A	Upon entry of the uniform UTI code, automated electronic prompts will appear on the GPs computer screen.	Provide the recommended antimicrobial treatment for a UTIs.	Remind the GP to collect urine samples and patients’ mobile telephone numbers.
	Intervention arm B		Provide the recommended antimicrobial treatment for a UTI and suggest delayed prescribing.	

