#### Computer prompt application

For intervention arms A and B, a computer prompt has been developed for use within the selected GP practice management software system. This prompt summarizes the recommendations for first-line antimicrobial treatment and will appear on the computer screen when the GP enters the International Classification of Primary Care code (U71) for 'cystitis, urinary infection, other’. In addition, for practices in intervention arm B, the prompt will include a recommendation to consider delayed antimicrobial prescribing. In intervention arms A and B this prompt will also remind the GP to collect patients’ mobile telephone numbers.

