## Discussion

### Anticipated outcomes

Utilizing a multidisciplinary perspective and social marketing conceptual framework, this study will contribute an understanding of the key behaviours and social norms that motivate change in GPs antimicrobial prescribing and patient antimicrobial consumption behaviours. The intervention will provide an evaluation of the different parts and thereby provide evidence to implement individual or all parts of the intervention beyond the study area and period.

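### Secondary objective 2 asks what delayed prescribing does to reconsultation, but the only stated comparator is control, which mixes delay with the package shared by arms A and B

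*Protocol article*

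**What the plan says.** All references are to the protocol article.

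- **Objective.** Secondary objective 2 is "To measure the uptake and impact of delayed antimicrobial prescribing for UTIs and the impact of this treatment approach on UTI GP reconsultation visits". It concerns one component of the intervention.
- **Arms.** Table 1 describes the arm B workshop as "In addition to the core components of interactive workshop A, the recommendation to delay antimicrobial prescribing for UTIs". Under Computer prompt application: "In addition, for practices in intervention arm B, the prompt will include a recommendation to consider delayed antimicrobial prescribing". The leaflet is extended in the same way. Audit and feedback go to both arms.
- **Reconsultation.** Its outcome section defines the measure (UTI revisits within one month of initial treatment) and names no comparator.
- **General rule.** Method of quantitative data analysis: "Outcomes will be compared between intervention (arms A and B) and the control arm", by multilevel logistic modelling.
- **Prescribing frequency.** Control is compared with each of arms A and B.
- **Consumption.** "The frequency of antimicrobial consumption will be compared between intervention arms A and B, according to their response to the text messages". The sample size section, however, sizes this outcome as control versus arm B and describes the detectable change as one achieved through delayed prescribing.
- **Anticipated outcomes.** The Discussion says the study will "provide evidence to implement individual or all parts of the intervention beyond the study area and period".

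**The concern.** Arm B differs from control by everything in arm A as well as by delay. Suppose reconsultation is compared with control and the result is offered as the answer to objective 2. Any effect of the workshop, audit reports or first-line prompt on return visits would then be attributed to delay, or could hide an effect of delay.

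The article itself gives reasons to expect a package effect. The Background states that feedback can reduce antimicrobial prescribing in Irish general practice. Patient messages about the harms of antimicrobials are offered in both intervention arms. The Economic evaluation links treatment failure from resistance to greater use of health care, so a shift in drug choice alone could alter return visits.

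The trial has randomised the arm that allows the question to be answered, but does not name that contrast for reconsultation.

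**Working it through.** **1. The plan's own figure for the delay outcome.** Inputs from the sample size section: 56% prescribed, a 20% decrease, 80% power, alpha 5% (two-sided assumed), ICC 1%, 20 practices (10 per arm).

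- Reading the decrease as absolute (56% to 36%), the two-proportion formula gives 97 per arm, or 107 with continuity correction.
- With m patients in each of 10 practices per arm, solve n × (1 + (m − 1) × 0.01) = 10m. Then m = 107 × 0.99 / (10 − 1.07) = 105.93 / 8.93 = 11.86, rounded up to 12. The total is 12 × 20 = **240**, as stated.
- Reading the decrease as relative (56% to 44.8%) gives about 900 to 980.

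So 240 reproduces, but for control versus arm B. No size or power is given for B versus A, which is the contrast the consumption analysis uses.

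**2. What each contrast estimates.** Let a be the effect of the shared package and d the further effect of delay, on the model's scale.

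| Contrast | Estimates |
|---|---|
| A − control | a |
| B − control | a + d |
| A and B pooled − control (equal weights) | a + d/2 |
| B − A | d |

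The general rule can be read as pooled or as arm by arm. Either way the result contains a.

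**3. Illustration on prescribing frequency.** Thirty practices in three arms give 10 per arm if allocation is equal (assumed). Feasibility gives 3,640 samples from 20 practices in six months, so 3,640 / 20 = 182 per practice, taken here as consultations of equal number in each practice. The design effect is 1 + 181 × 0.01 = 2.81, and the effective size per arm is 1,820 / 2.81 = 648. The baseline is 56%. The effects below are assumptions.

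| Package a | Delay d | B v control, probability of p < 0.05 | B v A, probability of p < 0.05 |
|---|---|---|---|
| 10 points | 0 | 95% | 5% |
| 5 points | 5 points | 95% | 44% |
| 5 points | 10 points | more than 99% | 95% |

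In the first row delay does nothing, yet B versus control is nearly always significant.

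**4. Precision.** Take the second row (56%, 51% and 46%). The 95% half-width for B versus control is 1.96 × √[(0.56 × 0.44 + 0.46 × 0.54) / 648] = 5.4 points. For B versus A it is 1.96 × √[(0.51 × 0.49 + 0.46 × 0.54) / 648] = 5.4 points. Precision is the same; power differs because d is smaller than a + d.

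**5. Reconsultation.** The article gives no baseline rate, so power cannot be worked out. Step 2 still applies: if the package alone raised reconsultation by 3 points (assumed) and delay added nothing, B versus control would show 3 points and B versus A would show 0.

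**The case against.** A reader might infer that the plan judges delayed prescribing only against control. The text does not support that.

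- **Consumption.** The plan names A versus B for it, and the Limitations section says follow-up of consumption is how the impact of delay is evaluated. For that outcome the isolating contrast is in place. What stands is the conflict with the sample size section.
- **Prescribing frequency.** Control versus each arm is the right comparison for secondary objective 1, the effect of the intervention. No passage says it measures delay, and since delayed scripts are counted within overall prescribing, it is a weak measure of delay. The point applies only where that comparison is interpreted as an effect of delay.
- **General wording.** The quantitative analysis section says data are compared between arms, which could include B versus A, and nothing forbids it. An article may also leave a list of contrasts to a fuller plan. But this article does name comparators for several outcomes, and its stated modelling rule points to control.
- **Whether the arms differ only in delay.** This is not settled. The section on patient educational material contrasts A1 and B2 with A2 and B1, by reference to a figure that is not shown. If the numbers denote periods, the timing of education also differs between arms. The Patient education section, which offers the iPad to all intervention practices at the start of Phase 3, suggests otherwise.
- **Component claim.** A reader might conclude that delay is the only component that can be evaluated. Patient education is also evaluated, by phase and by the A1/B2 contrast. What stands is narrower: the workshop and audit start together in both arms at Phase 2, and both arms also receive the prompt, so no randomised comparison separates them.

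**Conclusion.** The point holds for reconsultation under secondary objective 2. The section names no comparator, and the general rule supplies one that adds the shared package to the effect of delay. The consumption outcome has a related inconsistency: it is sized as control versus B and analysed as A versus B. The comparison of prescribing frequency with control is sound for objective 1, and the primary outcome is unaffected.

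The bias equals the package effect a, which the documents do not give. The 0 to 10 point range, equal allocation, equal practice sizes and an ICC of 1% for prescribing frequency are assumptions. That B versus control contains a follows from the arm definitions and needs none of them. That B versus A isolates delay depends on patient education being timed alike in both arms, or on period being allowed for.

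**What to change.** 1. For objective 2, name arm B versus arm A, from the same three-arm multilevel model, as the contrast for the effect of delayed prescribing on reconsultation, and on prescribing frequency wherever that is interpreted as an effect of delay.
2. Reconcile the sample size section with the consumption analysis: state which contrast measures delay, and what the 240 patients relate to.
3. Keep control versus each arm for objective 1, labelled as the effect of each full package.
4. If the timing of patient education differs between arms A and B, account for period in the B versus A contrast.
5. Under Anticipated outcomes, state that workshop, prompt and audit cannot be separated by the randomised comparison. The evaluation of patient education can stay.

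The cost is wording and one more secondary contrast from a model already planned; no new data are needed. Power for B versus A is below that for B versus control when delay adds less than the package does, so it should be reported with its confidence interval and a non-significant result not taken as absence of effect.
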